### Data collection

Study data will be collected and managed using REDCap (Research Electronic Data Capture) hosted by the University of the Witwatersrand. Data will be collected on the enrolled women, child and partners (where appropriate) at three stages: stage one, baseline at first research ultrasound visit at DPHRU < 25 weeks; stage two, 6-week postnatal follow-up; and stage three, 6-month postnatal follow-up. Data will be collected on tablets at stages one and two by two trained data collectors under the supervision of the study coordinator. At stage three, data will be collected by occupational therapists or physiotherapists trained in administering child development measures, under the supervision of the study coordinator. All data collectors will be trained on the principles of research ethics, Good Clinical Practice, referral procedures and management of difficult situations in the field.

Table 1 presents the schedule of enrolment, interventions and data collection.

**Table 1 Tab1:** Standard Protocol Items: Recommendations for Interventional Trials (SPIRIT) schedule of enrolment, interventions and data collection

	Study period				
	Enrolment	Intervention		Follow-up	
Timepoint	< 22 weeks GA	< 25 weeks GA	< 36 weeks GA	6 weeks postnatally	6 months postnatally
Enrolment					
Eligibility screen	X				
Informed consent	X				
Random allocation	X				
Interventions					
Early US		X			
Early US with messages		X			
Early and late US with messages		X	X		
Assessments: baseline and antenatal					
Socio-demographic questionnaire	X				
Fetal growth assessment		X	X		
Social support		X	X		
Maternal and paternal antenatal depression and anxiety		X	X		
Maternal and paternal antenatal attachment		X	X		
Maternal and paternal antenatal depression		X	X		
US experiences questionnaire		X	X		
Outcomes: primary and secondary					
Bayley Scales of Infant and Toddler Development, Third Edition					X
Home Screening Questionnaire					X
Mother/father–infant interaction					X
Perinatal and postnatal information				X	
Infant behaviour (crying, sleeping, etc.)				X	
Breastfeeding practices questionnaire				X	X
Maternal and paternal postnatal depression and anxiety				X	X
Social support				X	X
Partner involvement				X	X
Infant growth – weight and length				X	X
Immunisation status				X	X
Clinic attendance				X	X

*GA* gestational age, *US* ultrasound scan

The data collected at each stage is as follows:
*Baseline at first research ultrasound scan at DPHRU.* Data at the first research visit (< 25 weeks) will include the participant’s contact details, demographic characteristics and reproductive history, socio-economic status, social and instrumental support, and breastfeeding intentions. Maternal and paternal fetal attachment is assessed using the Maternal and Paternal Attachment Scales [44, 45], and the mother and her partner, if available, will complete a social support questionnaire and the Edinburgh Postnatal Depression Scale [46]. The woman and her partner, if available, will also be asked to complete an ultrasound experience questionnaire after the US.
*Six-week postnatal follow-up.* Two trained outcome assessors, blind to the mother’s arm allocation, will complete the follow-up questionnaires with the mothers, infants and partners, where available. Questionnaires will assess perinatal and postnatal information, breastfeeding practices, and partner and social support. Postnatal depression will be assessed for the mother and partner using the Edinburgh Postnatal Depression Scale. Infant growth will be assessed using standard procedures for infant weight and length (the SECA 416 infantometer for length and the SECA 367 infant scale for weight). Measures will be converted to *z*-scores using the 2006 WHO Growth Standards for LAZ, WAZ and WLZ. Birth weight and length as well as key information on maternal and infant birth outcomes will be collected from the infant’s Road to Health Booklet.
*Six-month postnatal follow-up.* Occupational therapists or physiotherapists trained in child development will complete the 6-month follow-up assessments with the mothers, infants and partners, where available. The primary outcome for the 6-month follow-up is child development as measured by the Bayley Scales of Infant and Toddler Development, Third Edition [47].

All of the study outcome measures are presented in Table 2.

**Table 2 Tab2:** Study outcome measures

Outcome	Instrument	Measure	Description	Method of aggregation	Timepoint
Primary outcome					
Child development at 6 months	Bayley Scales of Infant and Toddler Development, Third edition (Bayley III)	The total score from each developmental domain	Bayley III are an individually administered assessment of a child’s attainment of developmental milestones across five domains (i.e. cognitive, language, motor, social–emotional and adaptive skills) [47]. They have been recognised internationally as the most comprehensive tool to assess children from as young as 1 month old and have been validated in South Africa [48]	Individual scores to be compared between intervention and control groups using linear or logistic regression models dependent on the distribution of the data	End point
	Home Screening Questionnaire (HSQ)	HSQ score	The HSQ is a 30-item parent-report tool used to identify features of the home environments related to childhood development [49]. The HSQ has been validated and used for research purposes in a number of countries, including South Africa [50]	Individual scores to be compared between intervention and control groups using linear or logistic regression models dependent on the distribution of the data	End point
Secondary outcomes					
Mother/father–infant interaction at 6 months	Mother/father interaction rating scale	Interaction score	Rated from a 5-min videotape of mother/father and infant “talking and playing with each other”, with the infant in a high chair, the mother sitting on a chair at the same height opposite the infant and an attractive stack toy for them to share. We will use an adapted coding scheme developed by Richter et al. to code engagement (eye contact, joint attention), emotional tone, emotional regulation (maternal/paternal comforting for distress), maternal/paternal responsiveness and maternal/paternal scaffolding [51]	Individual scores to be compared between intervention and control groups using linear or logistic regression models dependent on the distribution of the data	End point
Infant growth at 6 weeks and 6 months	Weight and length	Weight (g) Length (cm) Weight-for-age *z*-score (WAZ) Length-for-age *z*-score (LAZ) Weight-for-length *z*-score (WLZ)	Infant growth will be measured using standard procedures for infant weight and length, and converted to *z*-scores using the 2006 WHO Growth Standards (WAZ, LAZ and WLZ)	Differences in mean weight and length of infants will be compared between intervention and control groups	Intermediate and end point
Breastfeeding practices at 6 weeks and 6 months	Maternal self-report questionnaire	Breastfeeding initiation and duration	Information on breastfeeding practices will be collected by trained interviewers using a semi-structured questionnaire	Categorical data will be presented as numbers and percentages. Changes in breastfeeding practices will be compared between intervention and control groups	Intermediate and end point
Maternal and paternal postnatal depression and anxiety during pregnancy, at 6 weeks and at 6 months	Edinburgh Postnatal Depression Scale (EPDS)	EPDS score	The EPDS is a screening tool for antenatal and postnatal depressive symptoms among women. The EPDS has been validated for use antenatally and postnatally in a number of settings, including South Africa [52, 53]	Proportion of mothers/partners showing signs indicative of depression will be compared during pregnancy, at 6 weeks and at 6 months. Data will be summarised by mean, SD and range at each time point	Baseline, intermediate and end point
Immunisation status and clinic attendance at 6 weeks and 6 months	Road to Health Booklet (child health record) or maternal/paternal self-report	Clinic attendance at routine child services (immunisation, growth monitoring, developmental screening, vitamin A, deworming). Other health contacts (e.g. sick child care)		Categorical data will be presented as numbers and percentages with comparisons in proportions made at 6 weeks and 6 months	Intermediate and end point
Partner involvement during pregnancy, at 6 weeks and at 6 months	Maternal/paternal self-report	Partner involvement in child care	Information on partner involvement in child care will be collected by trained interviewers using a semi-structured questionnaire	Categorical data will be presented as numbers and percentages with comparisons in proportions made at 6 weeks and 6 months	Baseline, intermediate and end point

*SD* standard deviation, *WHO* World Health Organization

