### Procedures

#### Recruitment

Approximately 500 women present to CHBH each month for their first pregnancy US, of which 50% are < 25 weeks gestation. This offers a potential pool of 250 women per month to be included in the study. Participants will be recruited from women attending the Foetal Medicine Unit (FMU) at CHBH, where routine fetal ultrasound examinations are conducted. Eligible women will be resident within Soweto, aged 18 years and older, with a singleton pregnancy and presenting < 25 weeks gestation. Major fetal abnormalities detected during the first routine ultrasound examination conducted by an experienced radiologist in the FMU, or severe maternal morbidities, will exclude a pregnant woman from the trial. These women will be transferred to specialised clinical services at CHBH, where she will receive appropriate treatment.

Sample size calculations were based on detecting a 0.5-standard deviation (SD) difference between arms on both the Bayley III Language and Cognitive Scales, and *z*-scores for weight-for-age (WAZ), length-for-age (LAZ) and weight-for-length (WLZ) measured at 6 months of age at 90% power, which is 85 per arm. Allowing for 15% potential attrition during pregnancy and during follow-up to 6 months of infant age, the sample size in each of the three arms will be 100. This makes a total sample size of 300 women for recruitment.

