### Data analysis

All available data at baseline will be analysed descriptively for each intervention group and in total. Categorical data will be summarised by numbers and percentages. Continuous data will be summarised by the mean, SD and range if data are normal and by the median, IQR and range if data are skewed. Minimum and maximum values will also be presented for continuous data. Differences regarding baseline variables will be checked for clinical relevance between the three treatment groups.

A CONSORT flow diagram will be used to summarise the number of participants who were: assessed for eligibility at screening, eligible at screening, eligible and randomised, lost to or discontinued the intervention and included in the primary outcome analysis. If possible, respondents and non-respondents will be compared.

The analysis of the primary outcome will be performed on the intention-to-treat population with no imputation of missing data. In the primary analysis, child development scores will be compared to the control group. If outcome data are normally distributed, we will fit linear regression models. If not normally distributed, outcome data will be categorised and logistic regression methods will be used to assess differences between intervention and control groups. Tests will be two-sided with a significance level of 0.05, and 95% confidence Intervals will also be reported. In case of relevant differences in baseline characteristics, additional adjustment(s) for these factors will be performed within the models to address potential confounding.

A stratified analysis will be done for three pair-wise comparisons—that is, Arm 1 vs. control, Arm 2 vs. control and Arm 1 vs. Arm 2 —according to the following subgroups: partner vs. no partner accompaniment and parity.

STATA, Version 15 (StataCorp, College Station, TX, USA) will be used for all analyses. Missing data and data from those who withdraw from the study will not be interpreted.

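### Table 2 lists five unranked Bayley domain scores and the HSQ as primary, compared with control in two arms at 0.05, while the 90% power covers one scale and one contrast

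*Protocol article*

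**What the plan says.** The protocol article touches the primary outcome in four places.

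- **Data collection, six-month follow-up:** "The primary outcome for the 6-month follow-up is child development as measured by the Bayley Scales", with no other instrument named. The abstract agrees that child development at 6 months is primary.
- **Table 2, primary block:** the Bayley III measure is "The total score from each developmental domain", and the instrument is described as covering "attainment of developmental milestones across five domains". The HSQ has its own row in the same block, above the row that opens the secondary outcomes. It is described thus: "The HSQ is a 30-item parent-report tool used to identify features of the home environments related to childhood development". For both instruments the analysis entry is the same: "Individual scores to be compared between intervention and control groups using linear or logistic regression models dependent on the distribution of the data".
- **Recruitment, sample size:** a 0.5 SD difference on "both the Bayley III Language and Cognitive Scales" and on three growth z-scores, at 90% power, gives 85 per arm, raised to 100 for 15% attrition. Table 2 lists the growth z-scores as secondary.
- **Data analysis:** child development scores are compared with the control group. "Tests will be two-sided with a significance level of 0.05". The Design section gives two intervention arms and one control arm.

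No domain is named as leading, and no composite, test order or division of alpha is stated.

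**The concern.** The article does not say which result decides the trial. Read as written, Table 2 yields ten primary tests (five domains in two arms against control), or twelve with the HSQ, each at 0.05. A single significant domain in a single arm could then be reported as a positive primary finding. The Discussion makes a later pragmatic trial depend on improvement in the outcome measures, so a chance result could carry that decision.

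The HSQ conflicts with the text in its own right. Table 2 files it under child development, yet describes it as a parent report on the home environment, and the six-month paragraph leaves it out of the primary outcome. The stated power was worked out for a smaller target than the primary set in Table 2.

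**Working it through.** **1. The plan's own figure.** Inputs from the Recruitment and Data analysis sections: difference 0.5 SD, two-sided alpha 0.05, power 90%, attrition 15%.

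n per arm = 2(1.960 + 1.282)² / 0.5² = 84.06, rounded up to 85. Then 85 / 0.85 = 100. Both figures reproduce. A one-sided 0.05 test would need 69, so 85 is the size for one scale and one pair of arms at an unadjusted two-sided 0.05.

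**2. Number of primary tests.** Five domains × 2 arms = 10. Adding the HSQ, 6 × 2 = 12.

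**3. Chance of at least one false positive.** If all tests were independent:

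- 10 tests: 1 − 0.95¹⁰ = 40.1%
- 12 tests: 1 − 0.95¹² = 46.0%

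The tests are not independent. The two contrasts share a control arm, which gives correlation 0.5 at equal arm sizes, and the scores come from the same child. The article gives no correlation between scores, so it is an assumption here, taken as equal for all pairs and varied. Simulation with three equal arms, no true effect and two-sided 0.05 per test (300,000 draws) gives:

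| Primary set | Corr. 0 | 0.5 | 0.7 | 0.8 |
|---|---|---|---|---|
| Five domains × 2 arms | 38% | 31% | 26% | 22% |
| Five domains + HSQ × 2 arms | 44% | 35% | 28% | 24% |
| Language and Cognitive × 2 arms | 17% | 16% | 15% | 14% |
| One score × 2 arms | 9% | – | – | – |

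At correlation 0.9 the first two rows fall to about 18% and 19%. Counting only false claims of benefit, they become 11-21% and 12-24% for correlations 0.8 to 0, against a nominal 2.5% for one two-sided test.

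**4. Power at 85 per arm.** Non-centrality = 0.5 × √(85/2) = 3.26. Two-sample t-test:

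| Two-sided level | Power |
|---|---|
| 0.05 | 90% |
| 0.025 | 84% |
| 0.05/4 = 0.0125 | 77% |
| 0.05/12 = 0.0042 | 64% |

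**5. Power of the two remedies,** for four tests (Language and Cognitive, each of Arms 2 and 3 against Arm 1):

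- *Holm.* The strictest step is 0.0125, so power for a true 0.5 SD effect is at least 77%. If all four effects are 0.5 SD, simulation gives about 85-87% per test for correlations between the two scales of 0.8 to 0.
- *0.025 per scale, arm contrasts in fixed order.* The first contrast has 84%. The second can succeed only if the first does; with both effects at 0.5 SD that gives about 75%.

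**The case against.** The strongest reply is that this is a condensed article and its analysis plan is not shown. A multiplicity method is commonly left to that plan, and a 0.05 level in the article does not exclude an adjustment. That stands as far as a missing correction goes. It does not settle what the article itself fixes: a primary block in Table 2 that disagrees with the text, unranked domains, and a power figure that fits neither version of the set.

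It is also fair that the sample-size paragraph does not define the primary outcome; it says which variables were powered. The direct conflict of definition is therefore the HSQ row. The sample size is a mismatch of coverage. The error range, too, depends on an assumed correlation and on counting any significant result as success, and the article states no success rule.

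Three stronger readings are tempting and are not supported:

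- A reader might add Arm 3 against Arm 2 to the count, which would raise the error rate further. The Data analysis section lists the three pair-wise comparisons only for the stratified analysis; the primary comparison is with control.
- A reader might infer that the intervention coaches parents on the very content of the HSQ. No HSQ items are shown. The Arm 2 messages concern the fetus and parental well-being, and the advice on talking, singing and responding to the infant's learning needs is described for Arm 3's second scan.
- A reader might take the phrase "both the Bayley III Language and Cognitive Scales" as a rule that both must be significant. In context it lists variables sized at 0.5 SD, together with the growth z-scores, and sets no joint criterion.

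**Conclusion.** The point holds. The article's primary set is inconsistent and unranked. Taken with a flat two-sided 0.05 and two arms against control, it implies a false-positive chance of about 22-38% for the Bayley domains and 24-44% with the HSQ. These ranges assume equal correlations between scores of 0.8 to 0, equal arms, and that any one significant primary test counts as a positive result. The conclusion does not depend on the HSQ: without it the rate is still more than four times 5% across that range. Even the two powered scales alone give 14-17%. The 90% power is correct for one scale and one contrast at unadjusted 0.05, and does not describe the primary set in Table 2.

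**What to change.** Make these changes before outcome data are examined by arm:

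1. Move the HSQ to the secondary block of Table 2, in line with the six-month follow-up text.
2. Name Bayley Cognitive and Language as the primary outcomes and make the other three domains secondary. This is one choice among several; its merit is that the sample size already rests on these two scales.
3. State how the error is controlled over the four primary tests: Holm, or 0.025 per scale with a written order for the two arm contrasts.
4. State what counts as a positive trial.
5. Restate power at 85 per arm and 0.5 SD. Under Holm: at least 77% per test, and about 85-87% if all four effects are 0.5 SD. Under the fixed order: 84% for the first contrast and about 75% for the second.

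The cost is wording, a less favourable stated power, and the loss of primary status for three domains. No extra participants are needed. The Trial status section reports recruitment complete in September 2019 and procedures due to end in July 2020, so the change should be dated, and if arm-level results had already been seen, that should be said.

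### The sample size rests on WAZ, LAZ and WLZ at 6 months, but the stated growth comparison names only mean weight and length

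*Protocol article*

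**What the plan says.** The sample size paragraph under Recruitment in the protocol article opens: "Sample size calculations were based on detecting a 0.5-standard deviation (SD) difference between arms on both the Bayley III Language and Cognitive Scales". It then adds z-scores "for weight-for-age (WAZ), length-for-age (LAZ) and weight-for-length (WLZ) measured at 6 months of age", and gives the result "at 90% power, which is 85 per arm". With the attrition allowance, "the sample size in each of the three arms will be 100".

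The infant growth row of Table 2 covers 6 weeks and 6 months. Its Measure column lists weight in grams, length in centimetres, WAZ, LAZ and WLZ. Its Description column says the measurements are converted to z-scores on the 2006 WHO standards. Its Method of aggregation column, where Table 2 states what is compared, says only: "Differences in mean weight and length of infants will be compared between intervention and control groups".

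The Data collection text on the 6-week visit repeats the conversion to z-scores but states no comparison. The Data analysis section describes regression for the primary outcome, sets the test level ("Tests will be two-sided with a significance level of 0.05"), and allows extra adjustment where baseline characteristics differ to a relevant degree. It has no separate rule for growth.

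**The concern.** The growth quantities that determine the sample size are not the ones named in the growth comparison. This is more than detail left to an analysis plan, because the article does state a comparison, and it differs from the one that was powered.

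Two things follow if the rule is applied literally.

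- **Precision.** Raw weight and length at a nominal 6-month visit vary with infant sex and exact age. The z-scores take that variation out. The adjustment clause in Data analysis would not obviously restore it: it is tied to baseline characteristics, baseline is the research visit before 25 weeks of gestation, and neither infant sex nor age at the postnatal visit is among the items listed for that visit.
- **Coverage.** WAZ and LAZ each have an obvious raw counterpart. WLZ relates the two measurements to each other, so neither mean weight nor mean length stands in for it. Under the literal rule, one of the three powered growth outcomes has no stated comparison.

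In addition, raw and standardised results could point in somewhat different directions, and the row does not say which carries the growth conclusion.

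**Working it through.** **Inputs from the protocol article.** Difference 0.5 SD, power 90%, 85 per arm, attrition 15%, 100 per arm recruited (all from Recruitment); two-sided 0.05 (Data analysis).

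**Step 1: reproduce the stated sample size.** For two means with a standardised difference of 0.5:

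n per arm = 2 × (1.960 + 1.282)² / 0.5² = 2 × 10.507 / 0.25 = 84.06, rounded up to 85.

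Power at 85 per arm is 90.3% by the normal approximation and 90.0% by the noncentral t. Inflating for attrition, 85 / (1 − 0.15) = 100. Both stated figures reproduce. A one-sided 0.05 test would need only 69 per arm, so the two-sided test is the one that was used.

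**Step 2: the same effect on the raw scale.** Let v be the share of raw variance due to sex and exact age. Hold the effect at 0.5 of the SD that remains once sex and age are removed, and compare raw means without adjustment. The standardised effect becomes 0.5 × √(1 − v), and the number needed for 90% power becomes 84.06 / (1 − v). The documents give no SD, no sex difference and no spread of visit age, so v is an assumption and is shown as a range.

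| v (assumed) | Effect in raw SD | Power at 85 per arm (t-test) | n per arm for 90% |
|---|---|---|---|
| 0 | 0.500 | 90.0% | 85 |
| 0.10 | 0.474 | 86.7% | 94 |
| 0.20 | 0.447 | 82.6% | 106 |
| 0.25 | 0.433 | 80.1% | 113 |

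The n column uses the normal approximation, as in Step 1. At v = 0.25 the loss is equivalent to analysing 85 × 0.75 = about 64 infants per arm.

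**Step 3: cross-check with a different parameterisation.** Let d be the sex difference in within-sex SDs (1:1 sex ratio) and a the SD of age-related variation in the same units. Raw variance is then 1 + d²/4 + a². Power by the normal approximation at 85 per arm:

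- d = 0.25, a = 0.1: variance 1.026, power 89.6%
- d = 0.5, a = 0.1: variance 1.073, power 88.2%
- d = 0.75, a = 0.2: variance 1.181, power 85.1%
- d = 1.0, a = 0.3: variance 1.340, power 80.4%

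These variances correspond to v of about 2%, 7%, 15% and 25% (v = 1 − 1/variance), so the two approaches agree. The loss is under one point at the low end and about ten points at the top.

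**The case against.** The strongest reply is that the rule is shorthand. The z-scores stand in the same row, the row's Instrument entry is itself weight and length, and Table 1 labels the whole growth outcome in the same words. On that reading the comparison covers all five listed measures, and nothing in the article says that raw values alone will be analysed. This stands as a real possibility, and it is why the point is a mismatch to reconcile and not proof that the z-scores will go untested. It works less well for WLZ than for WAZ and LAZ. It also sits uneasily with other Table 2 rows, where the same column says specifically what is compared; the depression row, for example, compares a proportion and summarises the score.

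A reader might go further and infer that the growth outcomes lack the claimed 90% power. The documents do not support that. The claim is made for the z-scores and is correct. The article claims no power for raw weight or length, and a true difference of 0.5 raw SD would also be detected with 90% power at 85 per arm. The loss arises only if the effect is fixed at 0.5 z-score SD and raw values are compared unadjusted, and its size depends on variance shares that the documents do not give.

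It is also fair that the choice among several secondary measures is often left to the analysis plan, which is not at hand. That would excuse silence; here a rule is stated, and it names other quantities than the sample size does.

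**Conclusion.** The mismatch holds. The sample size refers to WAZ, LAZ and WLZ at 6 months; the only stated growth comparison refers to mean weight and length, and WLZ has no raw counterpart in it. The sample size arithmetic is sound.

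The consequence is conditional and modest. On an unadjusted raw analysis of an effect of 0.5 z-score SD, power would lie between about 90% and 80% if sex and age account for 0% to 25% of raw variance. That range is an assumption, and at its low end the loss is negligible. Randomisation balances infant sex and visit age in expectation, so what is at stake is precision and clarity about which growth result counts. Growth is secondary; the primary Bayley III comparison is not affected. This is an inexpensive improvement, not a threat to the trial's main conclusion.

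**What to change.** Replace the Method of aggregation entry for infant growth in Table 2 with a rule along these lines: mean WAZ, LAZ and WLZ will be compared between arms by linear regression at 6 weeks and at 6 months, with 6 months as the time point to which the sample size refers; raw weight and length will be reported as supportive or descriptive results.

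This puts the comparison on the powered endpoints, gives WLZ a stated analysis and settles which scale carries the growth conclusion. The sample size stays at 85 per arm, 100 recruited. The cost is one line of text, since the measurements are already to be converted to z-scores.
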